### The Psychosocial Assessment Tool (PAT)

The Psychosocial Assessment Tool (PAT) [7, 8] is an evidence-based parent/caregiver report screener of family psychosocial risk in English and Spanish. The PAT generates a total score and 7 subscales (family structure, social support, child problems, sibling problems, family problems, stress reactions, family beliefs). Since the initial versions of the PAT [14–16], we have refined the PAT with the current all literacy version reflecting the broad assessment of family psychosocial risks. Screening with the PAT can be completed at diagnosis [17], can be used by multidisciplinary staff, and facilitates the delivery of psychosocial care [18]. Embedded in social ecology theory, the PAT total score maps on to the Psychosocial Preventative Health Model (PPPHM, Fig. 1) [19], a three-tier model which represents the distribution of psychosocial risks across the population of families. Most families experience some distress but have minimal risk factors (low levels of distress, few prior child, or family problems) and resources (financial resources, strong social support) that help them cope and adapt to their child’s illness (universal). A smaller group of families (targeted) have identified areas of risk and moderate resources. At the top of the pyramid are families with more severe problems, many risk factors, and few resources (clinical).

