**Fig. 2 Fig2:**
[figure not shown]
Interactive systems framework and stages of the implementation study

#### Aim 1

Refine strategies I (training) and II (TIER) using semi-structured interviews with stakeholders—parent advocates, multidisciplinary health care providers, national pediatric oncology professional organizations, and health care industry leaders (implementation team).

#### Aim 2

Compare the two theoretically based and empirically informed strategies to implement the PAT in English and Spanish using a cluster-randomized controlled trial. Compared to training:

**H2.1**. At the patient/family level, TIER will be associated with: (a) a higher proportion of families of newly diagnosed children screened and provided with feedback (penetration) and (b) higher rates of screening for ethnic minority and socioeconomically diverse families (health equity).

**H2.2**. At the provider level, TIER will be (a) more feasible and rated as appropriate and acceptable, (b) associated with greater engagement in addressing health disparities, and (c) associated with less burnout and better job satisfaction.

**H2.3**. At the institution level, TIER will be associated with: (a) a higher rate of site participation (adoption), (b) more positive perceptions of implementation benefits and fewer challenges (sustainability), and (c) psychosocial care better matched to need demonstrating a more equitable distribution of services and costs of care.

#### Aim 3

Based on the results of the trial and further guidance from the implementation team, we will integrate acceptable, feasible, and effective strategies to develop and disseminate a web-based PAT Implementation Toolkit.

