#### Procedure

All sites, regardless of randomization to strategy I or II, will participate in a 3-h professionally prepared webinar (develop educational materials, distribute educational materials) at the beginning of their cohort year. The webinar will include all information necessary to understand, access, and deliver the web-based PAT. The webinar will be based on our in-person training program and curriculum [35] modified to integrate feedback from aim 1 interviews. Each site PI, all screeners, and the research coordinator will participate. For sites randomized to strategy II, the champion will attend. We will work with sites to identify this team and the champion (in TIER) “individuals who dedicate themselves to supporting, marketing, and driving through an implementation, overcoming indifference or resistance that the intervention may encounter in an organization” [37].

After the PAT is completed online, it is scored immediately, and a summary of the score and clinical concerns identified is generated. Only coded data will be transmitted to the study data core. A master list for this data will be maintained at each respective study site and will not be shared with the core research team. We will provide support to sites in the technical aspects of the implementation related to using the web-based forms (centralize technical assistance). If we identify any pattern of problems with technical aspects of implementation, we will communicate with sites promptly.

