The outcomes at the institution level (Hyp 2.3) are as follows: adoption, the intention of sites to use the PAT (the ratio of sites that initiate the study); whether screening is perceived as an asset to the institution using the PAT Implementation Questionnaire (PIQ) [35] which will be completed by the site PI, the screeners, and the champion at T1, T2, and T3; whether services are matched to the needs of families based on PPPHM levels using EHR data using the Psychosocial Services and Medical Treatment Checklist (PSMTC) [18] at 30, 60, and 90 days; cost using the data from the PSMTC to estimate the amount of psychosocial staff time and national median hourly salary data [51–53]. The Intensity of Treatment Rating Scale (ITR-3) [54] will be completed at the 90-day post-screening data collection time point based on diagnosis, stage, and treatment.

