H2.1. ANOVA will compare the effectiveness of the two implementation strategies on penetration and health equity. The outcomes are proportions: families screened/families eligible, families provided feedback/families screened, ethnic minority families screened/ethnic minority families eligible, low SES families screened/low SES families eligible. ICCs among the clusters will be calculated and used to adjust for the cluster effect [67, 68].H2.2. Three sets of outcome variables—perception of implementation, engagement in addressing health disparities, and burnout/job satisfaction—will be tested. A two group analysis using Structural Equation Modeling (SEM) will compare the effectiveness of the two strategies [69, 70]. To test the effect of time, we will conduct latent growth curve analysis [71–73]. Analyses will be conducted using Mplus 5.0 [74] with ML estimation for outcome variables that meet the distribution assumptions, and WLSMV estimation for variables that do not. Potential mediating effects of favorable perception of implementation on provider job satisfaction and burnout will be examined using mediation models. TIER is expected to be associated with more favorable perceptions of implementation, less burnout, and higher job satisfaction.H2.3. At the institution level, adoption of the PAT will be measured by a ratio of sites that initiate implementation/sites that agreed (H2.3a). If substitutions are necessary, sites that are newly invited will be added to the denominator and adoption calculated by total acceptances/total invited. ANOVA will be conducted to compare the effectiveness of the two strategies. For H2.3b sustainability (PIQ perceptions of implementation benefits and challenges), ANOVA will be conducted to compare the effectiveness of the two strategies on benefits and challenges. For H2.3c, we are interested in the extent to which psychosocial care is matched to need. A cost-effectiveness threshold or criterion to which to compare costs of screening with these two implementation strategies has not been established, necessitating our consideration of valued outcomes in the psychosocial screening literature and resources available. We will use a data analytic approach that we used previously [18]. ANOVA will be conducted to test whether psychosocial care is matched with levels of psychosocial risks, resulting in a 2 (strategy) × 3 (psychosocial risks: clinical, targeted, universal) design on equitable distribution of services and costs of care. It is expected that the 3 PPPHM levels will be related to number and costs of services provided as measured on the PSMTC, with least at universal and most at clinical. It is expected that TIER will result in a better match between level of risk and services provided. Scores from the PSMTC will be derived and mapped onto the levels of the PPPHM. Additional analyses will be conducted to compare English speaking and Spanish speaking families, different ethnicity, race, and SES and insurance status on the outcome variables for H2.3c.

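### The H2.3c comparison of services, costs and care match can include only screened families, a group formed after randomisation, so it is not a randomised strategy effect over all eligible families

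*Protocol article*

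**What the plan says.** The Aim 2 analysis text for H2.3c specifies an ANOVA of strategy by risk level, "resulting in a 2 (strategy) × 3 (psychosocial risks: clinical, targeted, universal) design on equitable distribution of services and costs of care". The Specific aims word the hypothesis as a between-strategy claim at institution level: TIER will be associated with "psychosocial care better matched to need demonstrating a more equitable distribution of services and costs of care". Under Measurement/outcomes, the quantity assessed is "whether services are matched to the needs of families based on PPPHM levels using EHR data using the Psychosocial Services and Medical Treatment Checklist", at 30, 60 and 90 days.

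The section on the PAT gives the origin of the risk level: "the PAT total score maps on to the Psychosocial Preventative Health Model", a three-tier model. The Aim 2 Procedure says when a score exists: "After the PAT is completed online, it is scored immediately, and a summary of the score and clinical concerns identified is generated".

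Under H2.1, TIER is expected to produce "a higher proportion of families of newly diagnosed children screened and provided with feedback (penetration"), and the analysis text defines that outcome as "families screened/families eligible". Measurement/outcomes also says that race, ethnicity, zip code and insurance are reported for all eligible families as well as for those screened.

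**The concern.** A family that is never screened has no PAT score, so it has no risk level and no cell in the 2 × 3 design. Whether a family is screened is decided after its site has been randomised, and the trial expects the strategies to differ on exactly that. The H2.3c set is therefore selected by an outcome of the intervention.

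Two things are at stake. First, the screened families in the two arms may differ in need or in readiness to use services. Services and costs could then differ between strategies even if care were identical. Second, H2.3c is worded as an effect of strategy on how equitably an institution distributes care, whereas the analysis describes only the families each site managed to screen.

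**Working it through.** **1. Does the stated design leave room for unscreened families?**

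- The H2.3c factor has three levels: clinical, targeted and universal. There is no unscreened level.
- These are the tiers of the preventative health model, and the PAT section derives them from the PAT total score. The score is produced when a PAT is completed.
- The article also says that PSMTC scores will be mapped onto the same tiers. The PSMTC records services delivered. Using it as the measure of need would make matching circular, so it does not supply a risk level for an unscreened family.
- The phrase "will be completed at the 90-day post-screening data collection time point" belongs to the treatment-intensity scale. The PSMTC windows have no stated origin, so nothing here rests on timing.

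The only reading the stated risk measure allows is that H2.3c contains screened families alone.

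**2. Base.** The sample size text gives medians of 60, 92 and 339 new patients, with 6 sites of each size. 6 × (60 + 92 + 339) = 6 × 491 = 2946, and 2946 / 2 = 1473 per strategy. Both planned figures reproduce.

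**3. Families without a risk level.** The count per arm is 1473 × (1 − penetration). The article states no penetration, so the rates below are assumptions.

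| Assumed penetration, Training / TIER | No risk level, Training | No risk level, TIER | Overall |
|---|---|---|---|
| 50% / 70% | 737 | 442 | 40% |
| 60% / 80% | 589 | 295 | 30% |
| 70% / 85% | 442 | 221 | 22.5% |
| 80% / 90% | 295 | 147 | 15% |

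The loss is unequal between arms whenever H2.1 is true.

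**4. Illustration A: screening depends on need, care identical in both arms.** All inputs are assumed. Need U is standard normal, with tiers cut at the 60th and 90th percentiles. Expected services are 2 + 2U in both arms. The probability of being screened is 1 / (1 + exp(−(a + bU))), with a chosen to give 60% penetration in Training and 80% in TIER. The slope b runs from −0.3 to −1.0 in Training and is half that in TIER. Means among the screened come from numerical integration.

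| b (Training) | Mean services, Training v TIER | Apparent TIER excess | Clinical share, Training v TIER (truth 10%) | TIER − Training within universal, targeted, clinical | Clinical − universal gap, Training v TIER |
|---|---|---|---|---|---|
| −0.3 | 1.77 v 1.94 | 10% | 7.87% v 9.45% | 0.06, 0.02, 0.04 | 4.83 v 4.81 |
| −0.7 | 1.49 v 1.86 | 25% | 5.30% v 8.64% | 0.11, 0.05, 0.11 | 4.81 v 4.81 |
| −1.0 | 1.34 v 1.81 | 35% | 3.80% v 8.00% | 0.13, 0.07, 0.16 | 4.76 v 4.79 |

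The true difference is zero in every cell. The mean over all screened families is clearly distorted. (A simulated version with mean 1.33 rather than 1.34 puts the top of the range at 36%.) Within tiers little remains. The match contrast, the clinical-minus-universal gap, shifts by −0.02 to +0.03 on about 4.8, which is under 1%.

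**5. Illustration B: an unmeasured family factor also drives both screening and service use.** Penetration is assumed at 60% v 85%, and there is again no true effect. The false difference is about −0.30 to +0.30 services overall (SD 2.6) and about 0.10 to 0.24 in absolute size within tiers. The sign depends on which families are missed. The match contrast shifts by at most about 0.09 (−0.125 + 0.210) on a true gap of 4. The differences are about zero when screening is unrelated to service use, or when both penetration (70% v 70%) and the selection pattern are the same in the two arms.

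**The case against.** Several points on the other side have force.

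- **Reach is already analysed.** A reader might infer that a TIER gain in reach goes unseen because H2.3c ignores unscreened families. The article does not support that. H2.1 compares penetration over all eligible families, including ethnic minority and low-SES families. H2.3c asks a different question, whether care fits measured risk. This stands.
- **The planned contrast is conditional on risk level.** A reader might take the 10% to 35% excess as the bias in the planned care-match test. It is not. It belongs to the overall mean of services per screened family. Risk level is in the model, and the better-match prediction is a strategy-by-risk contrast that is almost untouched in Illustration A. This stands, and it limits the point. It does not remove it, because H2.3c also covers distribution and costs of services, and within-tier differences need not vanish (Illustration B).
- **No penetration figure exists.** The Background reports that 9 of 12 pilot centres implemented the web-based PAT. That is a rate of centres and cannot be read as the share of families screened.
- **This is a condensed article.** It never says in words that unscreened families are excluded. It cites a previously used analytic approach that is not shown, and handling of families without a score could sit in a fuller document. That is a fair defence against a charge of omission. The point rests instead on what the article fixes: the factor, its levels, the test and the between-strategy reading.

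**Conclusion.** The concern holds in a limited form. As specified, the H2.3c strategy comparison is confined to families with a completed PAT, a set formed after randomisation by the outcome H2.1 expects to differ between strategies. It is therefore not protected by randomisation and does not describe all eligible families.

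The size and direction of bias cannot be established from the document. The figures above show what could happen under assumed penetration, tier shares and selection patterns. They suggest that the overall mean of services is the vulnerable quantity, and costs with it if cost is proportional to services. Within-tier differences are small when need alone drives screening, and the match contrast is nearly unaffected. The documents do not show that the care-match test is seriously biased or that TIER's benefit is hidden. What should change is the scope of the conclusion, supported by a sensitivity analysis.

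**What to change.** In H2.3c:

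1. State that the 2 × 3 result applies to screened families only and is not a strategy effect over all eligible families.
2. Report it beside each arm's penetration from H2.1, so that the reader sees how much of each arm it covers.
3. Add an analysis weighted by the inverse probability of being screened, estimated within strategy from race, ethnicity, insurance and zip code.

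A measure over all eligible families, with unscreened families counted as not reached, is at most an optional supplementary description. It should not replace the strategy comparison. It would ignore whatever care unscreened families received, count penetration a second time, and need a per-family definition of matched care that the article does not give.

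The cost is a few sentences and modest programming. No new data are needed, provided the coded demographics on eligible families are held family by family rather than as monthly totals. The weighted analysis will have slightly wider intervals and corrects only for the demographics collected, so selection on unmeasured factors would remain.

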## Discussion

Family psychosocial screening, a Standard of Care, if implemented consistently and across children’s cancer programs can reduce disparities in care by facilitating care matched to need, and promote adaptation. The aim of this research is to implement universal, systematic family psychosocial risk screening with the PAT in English and Spanish to assure that *all* families of children newly diagnosed with cancer at the participating cancer centers are screened. Guided by the ISF for Dissemination and Implementation [36], this study will result in the development and broad dissemination of a PAT Implementation Toolkit for successful and sustainable implementation of universal, comprehensive, evidence-based family psychosocial screening for all families in pediatric oncology. As one of the few applications of implementation science in pediatric cancer, the results of this trial will provide valuable information about what strategies are effective in supporting comprehensive care. The broad theory proposed by the ISF is innovative in this field and provides a broad, forward looking approach to the process of advancing integrated care.

This project is ambitious and has some potential challenges. If a site that agreed to participate is unavailable, we have other eligible sites at each size to approach. We will retain the balance of sites from states with health disparity populations if we make substitutions. Second, to focus on population-based implementation, we did not consider sites with fewer than 30 new patients annually, and we selected sites with psychosocial staff at the median or above for their size. In addition, our selection criteria (minority population, psychosocial staff) precluded some sections of the USA, particularly less populated states with the smallest centers. Thus, we will not be able to generalize implementation to the smallest sites with fewer resources. However, we will distribute the PAT Implementation Toolkit to these sites and seek to evaluate the impact of broader dissemination of the Toolkit across sites of different sizes and different geographic locations. Finally, for cost-effectiveness, measuring the cost of psychosocial care is complicated and largely without precedent. Involvement of healthcare leaders in aims 1 and 3 will provide expert input in larger system level change to support family psychosocial risk screening and psychosocial care in pediatric cancer.

The importance of evidence-based psychosocial care for children with cancer and their families is recognized. However, too frequently, families of children with cancer do not receive this care, magnifying health disparities in our increasingly diverse pediatric oncology population. These inequities relate directly to screening for family psychosocial risks associated with social and relational determinants of health. Implementation of an evidence-based, parent report screener of family psychosocial risk across the social ecology in English and Spanish may address these health disparities. Risk screening initiates a process of preventive interventions across treatment. Universal, systematic screening assures that assessments are integrated and resources meet the needs of all children with cancer and their families.

## Data Availability

The datasets used during this study will be made available by the investigators on reasonable request.

## Abbreviations

AIM: Acceptability of Intervention Measure
ANOVA: Analysis of variance
AREA: Awareness, reflection/empowerment, action
COG: Children’s Oncology Group
EHR: Electronic health record
ERIC: Expert Recommendations for Implementing Change
ICC: Interclass correlation coefficient
IRB: Institutional Review Board
ISF: Interactive Systems Framework
ITR: Intensity of Treatment Rating Scale
NCORP: National Cancer Institute Community Oncology Research Program
PAT: Psychosocial Assessment Tool
PHI: Protected health information
PI: Principal investigator
PIPS-CSS: Preparing to Implement the Psychosocial Standards–Current Staffing & Services
PIQ: PAT Implementation Questionnaire
PPPHM: Pediatric Psychosocial Preventative Health Model
PSMTC: Psychosocial Services and Medical Treatment Checklist
REDCap: Research Electronic Data Capture
SEM: Structural equation modeling
SES: Socioeconomic status
StaRI: Standards for Reporting Implementation Studies
TIER: Training + Implementation Expanded Resources
WLSMV: Robust Weighted Least Squares
